	**Health Equity Implementation Framework (HEIF)**										
		Culturally relevant factors^d^ Clinical encounter^e^ Societal context^f^	Mixed methods approach to determine if HEIF factors are associated with uneven or disparate benefits to the intervention and to assess the implementation of THRIVE at a new site					Interviews with clinicians and administrators involved with THRIVE			8-week postintervention from the start of each sequence and at the study end
	**Exploration, Preparation, Implementation, Sustainment**										
		Adoption^g^ Active implementation^h^	Mixed methods approach to determine the adoption and implementation of THRIVE in a new site					Interviews with clinicians and administrators			8-week postintervention from the start of each sequence and at the study end
	**Proctor implementation outcomes**										
		Acceptability^i^ Appropriateness^j^ Feasibility^k^	Mixed methods approach to determine the Proctor implementation outcomes					Survey and interviews with clinicians and administrators			8-week postintervention from the start of each sequence and at the study end
		Fidelity^l^	Retrospective chart review					Standardized THRIVE checklist			Monthly

^a^ED: emergency department.

^b^Proportion of THRIVE referrals of those who are THRIVE eligible.

^c^Proportion of THRIVE participants experiencing the outcome within 30 days of discharge compared to usual care group.

^d^Organizational commitment to addressing disparities.

^e^Relative advantage of THRIVE to patients, degree of fit with existing practice, competing demands, and bias.

^f^Structures outside of the hospital that affect patient care.

^g^Organizational values, culture embedding, and championing adaption.

^h^Organizational priorities and goals and readiness for change and culture or climate.

^i^How fair or reasonable THRIVE is deemed.

^j^To what extent THRIVE seems suitable.

^k^The practicality and ease of delivering THRIVE.

^l^Fidelity to THRIVE’s core components.

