### Design and Randomization

#### Overview

This is a prospective single-site type 1 hybrid effectiveness-implementation pragmatic stepped wedge cluster RCT. Our stepped wedge design will include a sequential randomized rollout of the intervention to case managers at PAH in 3 steps, and data collection will occur over 18 months. This mixed methods (quantitative and qualitative) study design involves simultaneous collection and analysis of quantitative and qualitative data, giving priority weight to the quantitative data to evaluate program referrals, outcomes, and program fidelity, while qualitative data will evaluate the process through detailed descriptions of perspectives of barriers and facilitators faced by health care providers in implementing the THRIVE intervention [51]. This study includes qualitative interviews and surveys of clinicians and administrators to assess their perspectives on appropriateness, feasibility, and acceptability of THRIVE. Nesting the qualitative interviews within an RCT of the THRIVE intervention will allow us to determine whether the intervention improved primary outcomes (referrals to home care, 30-day readmission, ED use, and connection to primary care providers) and to identify professional and organizational barriers to implementation. Combining these insights with effectiveness outcome data will allow consideration for meaningful contextual factors that are considered critical to the implementation of THRIVE and subsequent outcomes.

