#### Randomization

Groups of case managers (4 in the first group, 4 in the second, and 5 in the third) were randomly assigned by the study methodologist to each sequence using a random number generator. A stepped wedge design—that is, a 1-time crossover design—was used for THRIVE (Table 2).

Specifically, following a baseline data collection period, 4 case managers will be randomized to receive training on the THRIVE clinical pathway. Following training, they begin referring to the THRIVE clinical pathway. At 8-week intervals, the remaining case managers will be trained in the THRIVE intervention and will be able to begin submitting referrals. Since case managers from the sequences work within the same space, the ability to conceal allocation was limited; however, all case managers were made aware of their upcoming ability to refer to the THRIVE clinical pathway.

**Table 2 table2:** Study design for the type 1 hybrid effectiveness-implementation stepped wedge cluster randomized controlled trial of the THRIVE clinical pathway.

Cluster	Baseline (3 months)	Enrollment period 1 (8 weeks)	Enrollment period 2 (8 weeks)	Enrollment period 3 (8 weeks)	Follow-up (18 months)
Sequence 1 (4 case managers)		✓	✓	✓	✓
Sequence 2 (4 case managers)			✓	✓	✓
Sequence 3 (5 case managers)				✓	✓

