### THRIVE Eligibility Criteria

Individuals eligible for a THRIVE referral include (1) being Medicaid insured, dually enrolled in Medicaid and Medicare, or Medicaid eligible; (2) residing in Philadelphia; (3) having experienced a hospitalization at the study hospital for more than 24 hours with a planned discharge to home; (4) agreeing to home care at partner home care settings; and (5) being aged 18 years or older. If home care services are declined at any time following discharge, THRIVE services are also discontinued. If palliative or hospice services are ordered following discharge, THRIVE services will not be offered.

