##### Outcomes and Measures

The primary outcome includes the referral rate to home care made by CMs compared to baseline and the nonrandomized cluster. The secondary outcomes are 30-day readmissions and ED visits. Additional covariate data at the patient (eg, demographics and comorbidities) and unit levels (eg, type of unit and discharging team or provider) will be collected from analyses. For THRIVE participants, these outcomes will be assessed from the date of hospitalization, which resulted in a referral to THRIVE. For the usual care group, we will identify all readmissions and ED visits occurring after the first index hospitalization identified in the EHR for the calendar year of the study. Outcome measures, guiding framework, data sources, collection, and timing are described in Table 3.

**Table 3 table3:** Summary of outcomes, measures, data sources, collection method, and timing.

Construct and framework					Design		Method of collection			Timing	
**Aim 1: Examine referral patterns, 30-day readmission, and ED^a^ use patterns for participants who receive THRIVE support services compared to those receiving usual care**											
	THRIVE referrals^b^ 30-day readmissions^c^ 30-day ED visits^c^ Primary care visit within 30 days of discharge^c^ Specialty care visit within 30 days of discharge^c^			Stepped wedge cluster randomized controlled trial		Electronic health record			Baseline and at the study end		
**Aim 2: Evaluate the implementation of the THRIVE clinical pathway, including fidelity, feasibility, appropriateness, and acceptability**											

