##### Analysis

We will develop monthly reports to monitor the referral patterns to the THRIVE clinical pathway. The target estimate and effect measure is the time-adjusted difference in participant outcomes [53,54]. The analysis of use outcomes (eg, 30-day readmissions and ED use) will use a mixed effects negative binomial regression model with random effects for the medical team and fixed effects for time to account for the stepped wedge cluster randomized design. Sensitivity analyses may be performed using logistic regression for health service use based on the distribution of the data. We will also examine the stability of effect estimates using generalized estimation equations with small sample adjustment, given the study design [55].

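### The primary referral outcome has two incompatible definitions, and the one in Table 3 is zero before crossover by construction

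*Protocol article*

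**What the plan says.** The outcomes text for Aim 1 states: "The primary outcome includes the referral rate to home care made by CMs compared to baseline and the nonrandomized cluster". The Overview of the design section agrees on the event, listing "primary outcomes (referrals to home care, 30-day readmission, ED use, and connection to primary care providers".

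Table 3 lists THRIVE referrals in the Aim 1 row. It assigns that row to the stepped wedge design, with measurement at baseline and at study end. Footnote b defines the measure as "Proportion of THRIVE referrals of those who are THRIVE eligible".

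The Randomization section fixes when a THRIVE referral can occur. For the first group, "Following training, they begin referring to the THRIVE clinical pathway". At each later step, "the remaining case managers will be trained in the THRIVE intervention and will be able to begin submitting referrals". Before crossover, "all case managers were made aware of their upcoming ability to refer to the THRIVE clinical pathway". Table 1 describes the hospital as a new site for the pathway.

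THRIVE eligibility has five criteria, of which the fourth is "agreeing to home care at partner home care settings". The Current Usual Care section says that usual care may or may not involve a home care referral.

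**The concern.** A trial needs one primary event, counted in one population that can be identified in both conditions. Here the text counts home care referrals without giving a denominator. The table counts THRIVE referrals and gives one. Footnote b is therefore the only operational definition in the article, and an analyst could reasonably follow it.

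Under footnote b, a comparison with baseline or with case managers still waiting would show that the pathway was switched on. It would not show whether case managers refer more patients to home care, which is the question in the text. The written denominator adds a second difficulty: accepting home care comes after being offered it, and the offer is the behaviour under study.

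**Working it through.** The Sample Size section gives totals for readmissions (472) and ED visits (534) and none for referral. There is no planned figure to reproduce, so the check sets the definitions side by side and then sizes the consequence.

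**Step 1. The two definitions**

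| | Outcomes text | Table 3 with footnote b |
|---|---|---|
| Event | Home care referral | THRIVE referral |
| Denominator | Not given | THRIVE-eligible patients |
| Possible before crossover? | Yes, under usual care | No, only after training |
| Comparison | Baseline and the nonrandomized cluster | None in the footnote; the table row gives stepped wedge design, baseline and study end |

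**Step 2. Control value under footnote b.** No one at a new site can submit a THRIVE referral before training. The numerator is 0 in every control cell, so the proportion is 0/n = 0% whatever n is.

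**Step 3. How little is needed to reject.** Take 267 patients per condition (the ED-visit figure, borrowed only for scale), a two-sided Fisher exact test and no allowance for clustering. With 0 events in control and k after crossover, p = 2 × C(267,k)/C(534,k).

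- k = 5: p = 0.061
- k = 6: p = 0.030, where 6/267 = 2.2%

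With rejection at 6 or more, the probability of rejecting is P(X ≥ 6), X ~ Binomial(267, π):

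- π = 2%: 44%
- π = 3%: 81%
- π = 5%: 99%

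Uptake of 5% of eligible patients would thus almost guarantee a positive result, even with no change in home care referral.

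**Step 4. The denominator.** Let o be the share of patients offered home care and a the share of those who accept. Among all otherwise eligible discharges, the home care referral proportion is o × a. Assumed values, not from the article: control 0.30 × 0.70 = 21%; after crossover 0.60 × 0.70 = 42%.

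| Numerator / denominator | Control | After crossover |
|---|---|---|
| Home care referral / criteria 1, 2, 3 and 5 | 21% | 42% |
| Home care referral / criteria 1 to 5, if acceptance is recorded only for those offered | 0.21/0.21 = 100% | 0.42/0.42 = 100% |
| THRIVE referral / THRIVE eligible | 0% | up to 100% |

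The same change of 21 points appears as 21 points, as 0, or as anything up to 100. The middle row rests on its stated assumption about recording. It shows that changing the numerator while keeping criterion 4 in the denominator may not be enough.

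**Step 5. Hypothesis 1 does not settle it.** It expects more referral for THRIVE participants than under usual care. The enrollment section says that patients, once identified, receive a home care referral, so a comparison of participants with usual care is also met by definition.

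**The case against.** **The home care outcome is sound.** The sentence that defines the primary outcome, and the Overview, both name home care referral, which can occur under usual care. A reader might infer from Table 3 that the whole primary comparison is empty. The article does not support that: only the table's version is degenerate. This objection stands.

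**Footnote b may be meant as an uptake measure.** Footnote c names usual care as comparator and footnote b names none. This is a fair reading, but the same table row assigns the measure to the stepped wedge design with a baseline assessment. The table is ambiguous at best.

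**The comparator exists.** A reader might infer that no nonrandomized cluster can exist, since all 4 + 4 + 5 = 13 case managers are randomised. But the Randomization section uses randomised for being moved into training, so the phrase plausibly means those not yet crossed over. Together with baseline, that is an ordinary stepped wedge comparison. Only the wording needs clarifying.

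**A model for referrals may exist.** The Aim 1 analysis section says "We will develop monthly reports to monitor the referral patterns to the THRIVE clinical pathway", and a reader might infer that nothing more is planned. Monitoring does not exclude modelling, and the detail may sit in an analysis plan that is not shown. No criticism is made on this ground.

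**Eligibility may be flagged before acceptance.** The enrollment section describes an automated flag, and the implementation strategies include a dashboard of eligible patients who were not referred. This puts the 100% against 100% scenario in doubt. It does not remove the problem, because the written criterion says otherwise and nothing says that the dashboard runs in control periods.

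**Conclusion.** Wrong as written. The primary referral outcome has two definitions that count different events, and the only one with a denominator has a control value of zero by construction. Under that version about 2% uptake is enough for nominal significance on the illustrative 267 per condition; clustering would change the exact threshold but not the structural zero.

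The contradiction and the zero rest on the article's text alone. The denominator concern is less certain: it follows from the literal eligibility criterion, and its size depends on how acceptance is recorded in control periods, which the article does not state. The conclusion does not extend to the home care referral outcome, which would be informative with a suitable denominator.

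**What to change.** Reconcile the Aim 1 outcomes text, Table 3 with footnote b, and the eligibility section:

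1. Make referral to home care at discharge the primary outcome in both text and table. State which home care agencies count, with the same rule in both conditions.
2. Use as denominator all discharges meeting criteria 1, 2, 3 and 5, whether or not the patient accepts home care. Identify them from the electronic health record in the same way in control and intervention periods, and attribute each to the responsible case manager.
3. State the contrast as case managers who have crossed over against those who have not, adjusted for time, and say that this is what the nonrandomized cluster means.
4. Report THRIVE referral among the eligible only after crossover, as a measure of uptake. State when eligibility is flagged relative to the home care offer.

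The cost is revised wording and one extraction. Table 3 already names the electronic health record as the source for this row, though the extraction must cover eligible discharges in control periods that were never referred.

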### Aims and Hypotheses

The specific aims of this research are to:

Examine referral patterns, 30-day readmission, and ED use patterns for participants who receive THRIVE support services compared to those receiving usual care.Hypothesis 1: We anticipate that referral patterns will increase and that 30-day readmissions and ED use will decrease for THRIVE participants compared to usual care.Evaluate the implementation of the THRIVE clinical pathway, including fidelity, feasibility, appropriateness, and acceptability.

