#### Enrollment in THRIVE

Enrollment in THRIVE begins with identification by CMs during hospitalization using a validated predictive algorithm developed by our team [31]. The algorithm is housed in the EHR and leverages principles of behavioral economics to “nudge” CMs to initiate a THRIVE referral. The THRIVE EHR flag was introduced to alleviate the need for CMs to manually identify THRIVE participants.

Once identified, THRIVE participants will receive a home care referral to Penn Medicine at home care services. The initial home care visit will be scheduled and completed by a nurse within 48 hours of discharge, at which time, medications are reconciled, discharge orders are reviewed, and person-centered goals of care are set. During the initial evaluation, home care nurses will determine the frequency of visits deemed necessary, with weekly visits ranging from 1 to 3 times depending on needs. Participants may receive additional services, such as speech or occupational therapy as required. All THRIVE participants receive a social work referral, their psychosocial needs are further assessed, and connections to community resources are provided. THRIVE participants receive a CHW referral as deemed necessary.

As a part of the THRIVE pathway, physician colleagues will extend continuity of care into the home following discharge to all THRIVE participants. Home care nurses will provide a brief patient status update to discharging physicians following the first home visit. During calls, nurses can raise questions about medications, clarify discharge orders, and receive guidance on emerging symptoms with the provider most recently involved with care. Extended supervision by discharging physicians will be provided for up to 30 days or until THRIVE participants have seen a primary care provider or specialist.

THRIVE participants will receive further support during discussions in our weekly interdisciplinary case management conferences for 4 weeks following discharge. During case management meetings, we will support connections to postacute primary, specialty care, behavioral health, and substance use services as needed. If a source of primary care is absent, we work to link THRIVE participants to community providers. Our intensive support addresses many of the social determinants of health that are known to influence health inequities such as housing, food insecurity, and limitations in access to behavioral health (Figure 1).

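### The primary referral outcome is named as home care referral but tabulated as THRIVE referral, which cannot occur in the control condition

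*Protocol article*

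**What the plan says.** The protocol article describes the referral outcome in several places.

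- **Aim 1, Outcomes and Measures (text):** "The primary outcome includes the referral rate to home care made by CMs compared to baseline and the nonrandomized cluster". Readmissions and ED visits are called secondary. The same paragraph refers the reader to Table 3 for measures, sources and timing.
- **Table 3, Aim 1 row:** the referral entry is THRIVE referrals. Footnote b defines it as "Proportion of THRIVE referrals of those who are THRIVE eligible". The design column gives the stepped wedge trial, and the timing is baseline and study end. There is no entry for home care referral.
- **Randomization:** for the first group, "Following training, they begin referring to the THRIVE clinical pathway". At later steps, "the remaining case managers will be trained in the THRIVE intervention and will be able to begin submitting referrals".
- **Current Usual Care:** discharge planning under usual care may or may not include a home care referral.
- **Enrollment in THRIVE:** "Once identified, THRIVE participants will receive a home care referral to Penn Medicine at home care services".
- **Design and Randomization, Overview:** the plan lists "primary outcomes (referrals to home care, 30-day readmission, ED use, and connection to primary care providers".
- **Aims and Hypotheses:** "We anticipate that referral patterns will increase and that 30-day readmissions and ED use will decrease for THRIVE participants compared to usual care". The term referral patterns is not defined there.

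**The concern.** The named outcome and the tabulated one are different quantities. A home care referral can happen with or without THRIVE. A THRIVE referral can happen only once a case manager has been trained, and training is what the trial randomizes. If Table 3's measure goes into the comparison that the text describes, the control periods supply zeros by design, and the contrast shows only that referral was switched on.

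What is at stake is the meaning of the primary result. Case managers might send through THRIVE only those patients whom they would have referred to home care anyway. The tabulated measure would still rise, although no additional patient had been referred to home care.

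The status of the other outcomes is also unsettled. Readmission and ED use are primary in the Overview and secondary in the outcomes section, so a reader cannot tell which result the trial rests on.

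**Working it through.** **No figure to reproduce.** The Sample Size section covers only readmissions (472) and ED visits (534). No rate, effect or power is stated for referral. The check therefore sets the two measures side by side, with assumed rates.

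**Step 1: values each measure can take.**

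| | Control (untrained case manager) | Intervention (trained case manager) |
|---|---|---|
| Footnote b: THRIVE referrals among eligible | 0 by design (Randomization) | 0 or more, depending on uptake |
| Outcomes text: home care referral rate | Above 0 is possible (Current Usual Care) | Usual referrals, plus THRIVE referrals, minus those replaced |

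The first contrast can be zero or positive, never negative. It is positive as soon as any referral is made.

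**Step 2: what each measure shows when THRIVE replaces usual referrals.** Let h be the home care referral rate under usual care, u the proportion referred to THRIVE after training, and s the share of THRIVE referrals that replace a home care referral which would have been made anyway. Each THRIVE participant gets a home care referral, so over a common denominator:

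- home care rate under intervention = h + u − s·u, where s·u cannot exceed h
- difference in home care rate = u − s·u
- difference on footnote b = u − 0 = u

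The article gives neither h nor u. Assume h = 30% and u = 30%:

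| Share replaced (s) | Footnote b, control to intervention | Home care rate, control to intervention | Difference in home care rate |
|---|---|---|---|
| none | 0% to 30% | 30% to 60% | 30 points |
| half | 0% to 30% | 30% to 30 + 30 − 15 = 45% | 15 points |
| all | 0% to 30% | 30% to 30 + 30 − 30 = 30% | 0 points |

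Other assumptions give the same pattern. With h = 50% and u = 10%, footnote b rises 10 points throughout, and the home care rate rises 10, 5 or 0 points. With h = 10% and u = 30%, at most 10 points can be replaced, so the home care rate rises by at least 30 − 10 = 20 points. That would be a genuine increase.

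**Step 3: how little uptake would look like an effect on footnote b.** This is an illustration only: the article plans no such test, and the calculation ignores clustering and time. The number of eligible patients per condition is not given, so take 40, 100 or 267. The value 267 is borrowed only as an upper size; in the Sample Size section it counts THRIVE participants, not eligible patients. Two-sided Fisher exact tests of 6 referrals against 0 give:

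- 40 per condition (uptake 6/40 = 15%): p = 0.026
- 100 per condition (6%): p = 0.029
- 267 per condition (2.2%): p = 0.030

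Five referrals against 0 give p = 0.055 with 40 per condition and p = 0.061 with 267. About six referrals would be enough, whether or not total home care referral had changed.

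**The case against.** The strongest reply is that the outcome labelled primary is sound. The text names the case managers' home care referral rate. Usual care can include such referrals, so the control value is not fixed at 0. The rate covers the case managers' patients and not only THRIVE participants, so the intervention value is not fixed at 100%. Under full replacement the difference is zero. Footnote b, unlike footnote c, mentions no comparison with usual care. The Analysis section speaks of monthly reports for THRIVE referral patterns and reserves its regression model for use outcomes. On this view footnote b is an adoption measure that nobody intends to test.

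Much of this stands, and it limits the point. A reader might infer more in three ways, none of which the article supports:

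- *That the primary result is positive whatever THRIVE does.* This fails on the outcome as worded in the text. Even on footnote b, case managers must make some referrals.
- *That the comparison is fixed at 100% for THRIVE participants.* This comes from joining the aim statements to the enrollment description. The aims leave referral patterns undefined and do not make home care referral among THRIVE participants the outcome.
- *That complete separation makes the effect impossible to estimate.* No regression of THRIVE referrals is specified. A difference in proportions can be estimated with zero control events, and the stated target is a time-adjusted difference.

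The reply does not remove the mismatch. The outcomes text sends the reader to Table 3, whose only referral measure is THRIVE referrals, placed within the stepped wedge design and timed at baseline and study end. It is also the only referral measure with a stated numerator and denominator.

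**Conclusion.** The point holds as an inconsistency in the primary outcome. The named measure is informative. The tabulated measure, if used in the stated comparison, has a control value of zero by design and would show an increase equal to uptake. In the worked case it shows 30 points where the change in home care referral lies anywhere from 0 to 30 points. That size rests on assumed rates. The zero control value rests only on the Randomization section.

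The home care measure is not neutral either. Every THRIVE referral carries a home care referral, so the measure contains a component of the intervention and leans toward an increase. It can still fail, but a rise would show more home care referral and not patient benefit.

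Separately, the Overview and the outcomes section disagree on whether readmission and ED use are primary, and they must be reconciled.

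**What to change.** State one primary outcome in the same words in Aims and Hypotheses, the design Overview, the Aim 1 statement, Outcomes and Measures, and Table 3:

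- **Numerator:** any home care referral order at discharge, to any agency, read from the EHR in the same way in both conditions.
- **Comparison:** by the case manager's randomized condition at the time of discharge.
- **Denominator:** one that depends neither on referral nor on agreeing to home care. An example is all adult Philadelphia residents who are Medicaid insured, dually enrolled or Medicaid eligible and are discharged home after more than 24 hours in hospital. The THRIVE-eligible group will not serve, because the eligibility criteria require agreement to home care, which lies close to the outcome itself.
- **Other outcomes:** give readmission, ED use and connection to primary care one status throughout.
- **THRIVE referrals among eligible patients:** report as an adoption measure for case managers who have crossed over, with no test against control.

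The cost is wording and one EHR field, assuming that home care orders to all agencies are recorded there; the EHR is already the Aim 1 data source. The downside is a smaller expected effect than on the THRIVE referral measure, because replaced referrals no longer count as gains.

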#### Implementation Strategies

We will use a series of implementation strategies to improve the effectiveness of THRIVE and promote its use [52]. These strategies will include (1) building and sustaining a coalition of diverse stakeholders through regular meetings and providing updates on THRIVE outcomes; (2) developing educational materials and conducting ongoing training of CMs, physicians, and advanced practice providers in the hospital and nurses and managers in home care using a scripted in-person training module to teach them about the elements of THRIVE and their role in implementing it; (3) auditing and providing feedback through the use of a referral dashboard to monitor all eligible THRIVE participants to document the individuals who were eligible for the intervention and not referred and providing feedback to case managers and document reasons for why referrals did not take place; (4) emailing reminders to case managers at weeks 2, 4, and 6; (5) identifying and preparing champions to promote the use of THRIVE; and (6) engaging of our advisory board to seek feedback for improvements.

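### As written, the denominator of the primary referral outcome counts only patients who agreed to home care, so it may not be comparable between control and intervention periods

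*Protocol article*

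**What the plan says.** **Outcome.** Aim 1, Outcomes and Measures, states: "The primary outcome includes the referral rate to home care made by CMs compared to baseline and the nonrandomized cluster". It gives no denominator.

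**Denominator.** Table 3, footnote b, defines the referral measure as "Proportion of THRIVE referrals of those who are THRIVE eligible". No other denominator for referrals appears in the article.

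**Eligibility.** THRIVE Eligibility Criteria opens with "Individuals eligible for a THRIVE referral include" and lists five conditions: (1) Medicaid coverage or eligibility, (2) Philadelphia residence, (3) a stay of over 24 hours with a plan to go home, (4) "agreeing to home care at partner home care settings", and (5) adult age.

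**Who acts.** Under Randomization, "Groups of case managers (4 in the first group, 4 in the second, and 5 in the third) were randomly assigned"; case managers start THRIVE referrals once trained. Under Enrollment in THRIVE, "Enrollment in THRIVE begins with identification by CMs during hospitalization using a validated predictive algorithm developed by our team".

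**Control condition.** Current Usual Care leaves home care referral optional in discharge planning. Sample Size says the comparison group comes from the EHR.

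**Monitoring.** Implementation Strategies describes a dashboard to "document the individuals who were eligible for the intervention and not referred" and to record why no referral was made.

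**The concern.** A referral rate tests whether training changes case manager behaviour only if its denominator is fixed before that behaviour occurs. Criterion 4 is not fixed in that way. A patient can agree to home care only after someone raises it, and raising it is part of the discharge planning that the intervention aims to change. Conditioning on agreement therefore conditions on a step that follows randomization.

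The step may also be unevenly observed. Under usual care some patients will be asked about home care and others need not be. The article does not say that agreement or refusal is recorded for EHR-derived control patients. Criterion 4 could then drop unasked control patients, or it could be applied only after training. In either case the comparison with baseline and with case managers not yet crossed over would not be between like populations. The outcome affected is the primary one and the first element of Hypothesis 1.

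**Working it through.** **The plan's own figure.** There is none to reproduce. The sample sizes of 472 and 534 concern readmissions and ED visits, and no rate or power statement is given for referrals. The check is a tracing of definitions followed by an illustration.

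**Step 1: trace the definition.** The primary outcome text has no denominator. Table 3, footnote b, supplies one: the THRIVE eligible. The eligibility section defines those people by five criteria, of which the fourth is agreement to home care.

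**Step 2: separate the criteria by timing.** Criteria 1, 2 and 5 are patient characteristics. Criterion 3 is set in hospital, partly by discharge planning, but needs no home care offer. Criterion 4 cannot be met without one.

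**Step 3: what conditioning on agreement does.** Let *N* be discharges meeting criteria 1, 2, 3 and 5, *o* the share offered home care, *q* the share of offers accepted, and *r* the share of accepters referred.

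- Denominator with criterion 4: *N·o·q*
- Home care referrals: *N·o·q·r*
- Rate with criterion 4: *N·o·q·r / (N·o·q) = r*
- Rate without criterion 4: *N·o·q·r / N = o·q·r*

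The first rate does not contain *o*, so a change in how often home care is offered cannot move it.

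**Step 4: numbers, all assumed.** Take *N* = 1000 per period and *r* = 0.90. The numerator is home care referrals, as in Outcomes and Measures.

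| Period | *o* | *q* | Agree | Referred | Rate with criterion 4 | Rate without |
|---|---|---|---|---|---|---|
| Control | 0.40 | 0.60 | 240 | 216 | 216/240 = 90.0% | 216/1000 = 21.6% |
| After training | 0.80 | 0.60 | 480 | 432 | 432/480 = 90.0% | 432/1000 = 43.2% |
| After training, lower acceptance | 0.80 | 0.50 | 400 | 360 | 360/400 = 90.0% | 360/1000 = 36.0% |

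- Criterion 4 in both periods: the difference is 0 points. Without it, the difference is 43.2 − 21.6 = 21.6 points, or 36.0 − 21.6 = 14.4 with lower acceptance.
- Criterion 4 only after training: 90.0 − 21.6 = 68.4 points, against 21.6 without it.

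These lines pair the numerator in the text with the denominator in Table 3, a pairing the article does not spell out.

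**Step 5: footnote b taken literally.** Its numerator is THRIVE referrals, which start only after training, so the control numerator is about 0. If all 432 later referrals were THRIVE referrals, the contrast would be 432/480 − 0/240 = 90.0 points with criterion 4 and 432/1000 − 0/1000 = 43.2 points without it. On this reading the control value is fixed by design, so the contrast does not measure a change in home care referral. The numerator needs settling along with the denominator.

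**The case against.** **The dashboard and flag point to a wider pool.** The dashboard counts people who were eligible but not referred and keeps the reasons, and the EHR flag spares case managers from finding patients by hand. Both suggest a list that exists before agreement. This is the strongest reply and may describe actual practice. It does not settle the matter, because neither section says criterion 4 is left out, and the eligibility section includes it.

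**Two measures are being combined.** Outcomes and Measures counts home care referrals; footnote b counts THRIVE referrals. This stands. The masking example therefore cannot come from footnote b alone, and the numerator belongs in the correction.

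**A condensed article leaves query details elsewhere.** That would answer an omission. Here the denominator and the eligibility list are both stated, and the difficulty comes from reading them together.

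**Stronger readings a reader might infer.**
- That the rate is driven towards 100%. This needs nearly everyone who agrees to be referred, which the article does not say. A dashboard of eligible patients not referred shows the team expects a lower ratio.
- That audit feedback lets case managers remove patients by recording a refusal. No section says refusals leave the denominator; reasons for non-referral are to be documented.
- That control patients were never asked. Usual care may include home care, so some were.

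**The remedy is imperfect.** Criterion 3 is also partly a product of discharge planning. This is true and remains a limitation.

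**Conclusion.** The concern holds as a defect in how the primary outcome is defined. On the stated wording, the referral denominator depends on an offer and an acceptance that the randomized case managers influence and that usual care does not require. Comparability between control and intervention periods is not assured.

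The documents do not establish a size or a direction. The differences of 0, 21.6 and 68.4 points rest on assumed offer, acceptance and referral shares and on a numerator and denominator taken from different places. They show only that the effect could be hidden or exaggerated, depending on how criterion 4 is applied. The conclusion assumes that eligibility in footnote b means the five listed criteria. If the working list already omits criterion 4, the denominator needs only a clarifying sentence, but the numerator must still be reconciled.

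**What to change.** Before referral data are analysed:

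1. Define the primary denominator as all discharges meeting criteria 1, 2, 3 and 5, identified by the same EHR query in baseline, control and intervention periods and attributed to the responsible case manager.
2. Keep agreement to home care as a condition for receiving THRIVE only. Report refusals as a separate count by period.
3. Use one numerator that can occur in both phases: home care referrals, as in Outcomes and Measures. Amend footnote b to match, and report THRIVE referrals after training descriptively.
4. State how patients with palliative or hospice orders after discharge are counted, with the same rule in every period.

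**Cost.** This needs revised wording and a common query; no patient's care changes. The article does not describe the EHR fields, so the effort of attributing discharges to case managers cannot be judged from it. The reported rate will be lower because refusals stay in the denominator. Criterion 3 still depends partly on discharge planning, so the share of discharges planned for home should be shown by period.
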